### 2.11. Sample Size

The minimum sample size was calculated based on the expected improvement in overall QoL (decrease in points) and BMI (decrease in kg/m^2^) after the six-month follow-up and the expected difference between the experimental and the control group. A decrease in overall QoL and BMI with a 50% difference between groups (in the experimental/control group, a decrease by 20/10 points and 2.0/1.0 kg/m^2^, respectively) was assumed. For this calculation, a 5% significance level and 80% power were considered. The sample size required at baseline is approximately 100 respondents (for the experimental/control group: 50/50 for overall QoL and 42/42 for BMI), including a 20% drop-out rate at the end of the study. When the data collection is completed, the adequacy of the study sample will be checked by applying the post hoc statistics to calculate power.

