### 2.7. Quality of Life (QoL) 

To assess QoL, a thyroid-specific questionnaire (ThyPRO) in a Polish version (ThyPROpl) will be applied [32]. There is substantial evidence for the clinical validity and reliability of the questionnaire in patients with mild thyroid disorders [33,34]. The ThyPRO consists of 84 items summarized in 13 scales as well as a single item measuring the overall impact of thyroid disease on QoL within the last four weeks. The questionnaire covers physical symptoms specifically relevant to thyroid diseases (e.g., symptoms of hyperthyroidism and goitre) and non-specific aspects of high importance to patients with thyroid diseases (e.g., fatigue). Responses for each item will be scored with points on a five-point Likert scale as follows: ‘not at all’ (0 points), ‘a little’ (1 point), ‘some’ (2 points), ‘quite a bit’ (3 points), and ‘very much’ (4 points). The average score of items in a scale will be divided by four and multiplied by 100 to yield 13 scales ranging from 0 to 100 points [32,33], with higher point scores indicating a worse quality of life related to each scale.

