### 2.12. Statistical Analysis

Categorical variables will be presented as a sample percentage (%) and continuous variables will be presented as means with a 95% confidence interval (95%CI) or medians with an interquartile range (IQR) for variables with normal or non-normal distribution, respectively. To assess the impact of dietetic counseling and verify the differences between the experimental and the control group, two-tailed tests will be applied; *p*-values < 0.05 will be considered significant. 

The normality of variable distribution will be verified with a Kolmogorov–Smirnov test before the statistical analysis. For continuous variables, e.g., diet quality scores, AdhS, scores of QoL, nutrition knowledge score, TFTs, markers of adiposity, metabolic parameters, and changes after a six-month follow-up with respect to baseline will be verified with a T-test for dependent samples or a Mann–Whitney test, for variables with normal or non-normal distribution, respectively. For categorical variables, logistic regression modeling will be applied to determine the chance of the occurrence of high diet quality, high AdhS, high QoL, as well as low adiposity and elevated metabolic parameters. The odds ratios (ORs) and 95% confidence intervals (CIs) will be calculated. The significance of ORs will be verified with Wald’s statistics. A crude model and models with an adjustment for confounders will be created. All analyses will be performed with Statistica software (version 13.3 PL; StatSoft Inc., Tulsa, OK, USA; StatSoft, Krakow, Poland).

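### The planned post hoc power check cannot show whether the sample was adequate, and the 80% power cannot be verified because neither the overall QoL score nor any SD is stated

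*Protocol article*

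**What the plan says.** Section 2.11 of the protocol article sizes the trial on two outcomes at six months, overall QoL and BMI. The assumed mean changes are "in the experimental/control group, a decrease by 20/10 points and 2.0/1.0 kg/m^2^, respectively", so the planned between-group differences are 10 points and 1.0 kg/m². It adds that "a 5% significance level and 80% power were considered". After a 20% allowance for drop-out it arrives at 50 per arm for QoL and 42 per arm for BMI; QoL therefore sets the total of about 100. The section closes by promising that, once the data are in, "the adequacy of the study sample will be checked by applying the post hoc statistics to calculate power".

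Section 2.12 fixes the sidedness of the analysis: "two-tailed tests will be applied; *p*-values < 0.05 will be considered significant".

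Section 2.7 describes the QoL instrument as 13 scales "as well as a single item measuring the overall impact of thyroid disease on QoL within the last four weeks". Each item is scored 0 to 4. The conversion (item average divided by four, times 100) is stated "to yield 13 scales ranging from 0 to 100 points". No conversion is stated for the single overall item, and no composite across scales is defined.

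**The concern.** The only safeguard that section 2.11 offers for its sample size is the post hoc power calculation. If this uses the effect seen in the data, it adds nothing to the p-value. A null result would look underpowered even where the confidence interval excludes the planned benefit, and a reader could take a precise negative trial for an inconclusive one.

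The planning calculation cannot be checked in its place. It gives effects, significance level, power, drop-out and the resulting numbers, but not the SD of change, which decides the power. The outcome that sets the trial size is also expressed in points on a scale that the article does not define.

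**Working it through.** **1. Reproducing the stated numbers.** Inputs from section 2.11: differences of 10 points and 1.0 kg/m², 5% level, 80% power, 20% drop-out, 50 and 42 per arm. Two-sidedness comes from section 2.12. The sample size cannot be computed forward without an SD, so solve for it. Assumptions: a two-sample t-test on the change, and drop-out applied as n/(1 − 0.20).

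- QoL: completers per arm = 50 × 0.8 = 40. At n = 40 per arm, 80% power needs a standardized difference d = 0.634. SD = 10/0.634 = 15.8 points. Back-check: 40/0.8 = 50, as stated.
- BMI: 42 × 0.8 = 33.6, so take 33 completers. At n = 33, d = 0.700 and SD = 1.0/0.700 = 1.43 kg/m². Back-check: 33/0.8 = 41.25, rounded up to 42, as stated.

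The stated numbers are therefore internally coherent. The SDs are inferred, however. Other conventions for sidedness and drop-out move the implied QoL SD from 15.8 up to about 20.

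**2. How far power depends on the missing SD.** At 40 per arm and a 10-point difference (two-sided t-test; the SDs are illustrations, none comes from the article):

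| SD of change | Power |
|---|---|
| 12.5 | 94% |
| 15 | 84% |
| 16 | 79% |
| 20 | 60% |

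**3. The QoL scale.** The only overall measure in section 2.7 is the single item. Scored 0 to 4, it can fall by at most 4, so neither 10 nor 20 points is possible on it as written. The 0–100 conversion would make such falls possible, but it is stated for the 13 scales only. Either the item was meant to be rescaled, or another summary was meant; the text does not say which.

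**4. What observed power measures.** With z_p the two-sided normal quantile of the p-value, power at the observed effect is Φ(z_p − 1.96) + Φ(−z_p − 1.96). It depends on p alone:

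| p | Observed power |
|---|---|
| 0.01 | 73% |
| 0.05 | 50% |
| 0.20 | 25% |
| 0.50 | 10% |

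Reaching 80% needs z_p = 1.96 + 0.84 = 2.80, which is p of about 0.005.

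**5. Why that cannot show adequacy.** Take two hypothetical QoL results with 40 per arm and p = 0.20 (normal approximation, z = 1.28).

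- SD 15.8: SE = 15.8 × √(2/40) = 3.53; estimate = 1.28 × 3.53 = 4.5; 95% CI = 4.5 ± 1.96 × 3.53 = −2.4 to 11.4. A 10-point benefit is not excluded.
- SD 7.9 (half, for illustration): SE = 1.77; estimate = 1.28 × 1.77 = 2.3; 95% CI = 2.3 ± 3.5 = −1.2 to 5.7. A 10-point benefit is excluded.

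Observed power is 25% in both. The confidence interval separates the two cases; the power figure does not.

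**The case against.** The article does not say which effect the post hoc calculation will use. Power for the planned 10 points, with the SD and numbers actually obtained, would not be circular. That is correct, and the criticism holds only for the observed-effect reading. That reading is the natural one for the wording, and a sentence that allows both needs to be settled. It is also true that no decision in sections 2.11 or 2.12 hangs on the check, which limits the harm to interpretation.

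A second objection is that an unreported SD in a condensed article may stand in the full protocol, and that the arithmetic holds once an SD is inferred. This stands as far as it goes: there is no arithmetic error, and the missing SD alone would be a minor reporting point. The mismatch between sections 2.7 and 2.11 on the QoL score is different, because it lies in what the article does say.

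Three stronger readings are tempting and are not supported:

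- A reader might infer that true power is well below 80%. The documents give no SD, and values below 15.8 raise power (94% at 12.5).
- A reader might argue that the overall item, rescaled, moves in 25-point steps and so must have a larger SD. This needs both that overall QoL is the single item and that it is rescaled; section 2.11 says neither. Even then, means of −20 and −10 allow a pooled SD as low as 11.2.
- A reader might say that the check would pass every positive result. It would not: results with p between about 0.005 and 0.05 show observed power of 50% to 80%, short of the planned level.

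**Conclusion.** The concern holds in a limited form. On its natural reading, the post hoc power check is a one-to-one function of the p-value: every non-significant result shows less than about 50%, whatever the precision, so it cannot establish that the sample was adequate. Separately, the 20- and 10-point falls in overall QoL match no overall score that section 2.7 defines, and the 80% power cannot be verified because no SD is given.

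The stated 50 and 42 per arm are consistent with SDs of change of about 15.8 points and 1.43 kg/m², provided a two-sided two-sample t-test and 20% drop-out were used. The numbers are unverifiable, not shown to be wrong, and no shortfall in power is demonstrated.

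**What to change.** In section 2.11:

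- Delete the post hoc power sentence. State instead that adequacy will be judged by the 95% CI of the difference in change between the QDP and CDC groups, read against 10 points for QoL and 1.0 kg/m² for BMI. If a power check is kept, specify that it uses the planned difference with the pooled SD, not the observed effect.
- State the SDs of change actually used for both outcomes, with their source, and show how power varies around them. The back-solved 15.8 and 1.43 serve to check consistency and should not be adopted as the sponsor's assumptions unless they were.

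In section 2.7, name the score that overall QoL refers to and give its range and any conversion, so that the 20- and 10-point falls have a defined scale.

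The cost is wording only. No additional participants, visits or measurements are needed.

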### 2.12. Statistical Analysis

Categorical variables will be presented as a sample percentage (%) and continuous variables will be presented as means with a 95% confidence interval (95%CI) or medians with an interquartile range (IQR) for variables with normal or non-normal distribution, respectively. To assess the impact of dietetic counseling and verify the differences between the experimental and the control group, two-tailed tests will be applied; *p*-values < 0.05 will be considered significant. 

The normality of variable distribution will be verified with a Kolmogorov–Smirnov test before the statistical analysis. For continuous variables, e.g., diet quality scores, AdhS, scores of QoL, nutrition knowledge score, TFTs, markers of adiposity, metabolic parameters, and changes after a six-month follow-up with respect to baseline will be verified with a T-test for dependent samples or a Mann–Whitney test, for variables with normal or non-normal distribution, respectively. For categorical variables, logistic regression modeling will be applied to determine the chance of the occurrence of high diet quality, high AdhS, high QoL, as well as low adiposity and elevated metabolic parameters. The odds ratios (ORs) and 95% confidence intervals (CIs) will be calculated. The significance of ORs will be verified with Wald’s statistics. A crude model and models with an adjustment for confounders will be created. All analyses will be performed with Statistica software (version 13.3 PL; StatSoft Inc., Tulsa, OK, USA; StatSoft, Krakow, Poland).

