The research hypotheses are:Dietetic counseling with the use of a qualitative dietary protocol can facilitate patient understanding and long-term adherence to dietary recommendations compared to conventional dietetic counseling.A well-composed diet supported with a simple, qualitative dietary protocol, by improving food selection and diet quality, can improve the quality of life of HT subjects, reduce adiposity, and improve metabolic parameters. Furthermore, a better effect of a qualitative dietary protocol than conventional dietetic counseling is possible.

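### The trial is sized on two unranked endpoints and calls any p<0.05 significant across about 33 outcomes, so the stated rule does not hold the 5% level for a claim that QDP beats CDC

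*Protocol article*

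**What the plan says.** Section 2.11 (Sample Size) rests on two endpoints: "The minimum sample size was calculated based on the expected improvement in overall QoL (decrease in points) and BMI". The assumed changes are "in the experimental/control group, a decrease by 20/10 points and 2.0/1.0 kg/m^2^, respectively". For both, "a 5% significance level and 80% power were considered", and the resulting baseline numbers are "for the experimental/control group: 50/50 for overall QoL and 42/42 for BMI", "including a 20% drop-out rate at the end of the study". Neither endpoint is called primary there or elsewhere. Nothing says whether success needs both or either.

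Section 2.12 (Statistical Analysis) gives the decision rule for comparing the arms: "two-tailed tests will be applied; *p*-values < 0.05 will be considered significant". The continuous outcomes it names are diet quality, adherence, QoL, nutrition knowledge, thyroid tests, adiposity and metabolic parameters, with no ranking. It adds crude and adjusted logistic models, with Wald tests, for categorised diet quality, adherence, QoL, adiposity and metabolic parameters.

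The second hypothesis in section 1.1 is that a well-composed diet supported by the QDP "can improve the quality of life of HT subjects, reduce adiposity, and improve metabolic parameters". It adds that a better effect than conventional counselling is possible, without saying which result would decide that.

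**The concern.** Two endpoints each carry their own 5% test, and a single p<0.05 rule covers every outcome family. If no outcome is designated to decide the QDP-versus-CDC question, a report that follows the plan exactly may point to whichever comparison crosses the line. The 5% used for the sample size would then not be the error rate of the trial's comparative claim.

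This is more than detail left to an analysis plan. The article itself fixes the significance rule and builds the sample size on two endpoints without ranking them. Section 3.3 also says that a causal effect of the intervention can be demonstrated, so the work is not presented as exploratory.

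**Working it through.** **Plan's own figure.** No standard deviation is given, so 50 and 42 per arm can be neither confirmed nor refuted. Back-solving a two-sample comparison at two-sided 5% and 80% power, with dropout applied as n/(1−0.2):
- QoL, difference 20−10 = 10 points: 50 per arm implies 40 completers and an SD of about 15.8–15.95 points.
- BMI, difference 2.0−1.0 = 1.0 kg/m²: 42 per arm implies 33 completers and an SD of about 1.43–1.445 kg/m².

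QoL is therefore the endpoint that fixes 50 per arm.

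**Count of outcomes.**
- Diet quality (2.5): pHDI, nHDI = 2
- QoL (2.7): 13 ThyPRO scales plus the single overall item = 14
- Nutrition knowledge (2.8) = 1
- Adiposity (2.9): weight, BMI, waist, waist-to-height ratio, body fat, skeletal muscle index = 6
- Thyroid (2.10): TSH, FT4, FT3, TPOAb, TgAb = 5
- Metabolic (2.10): SBP, DBP, glucose, triglycerides, cholesterol = 5

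Total 2+14+1+6+5+5 = 33. The adherence score is left out because only the QDP arm keeps diaries. Outcomes named in the second hypothesis: 14+6+5 = 25.

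**Model.** No true difference; each outcome is one between-arm two-sided 5% test at six months. If independent, the chance of at least one false difference in either direction is 1−0.95^k, and of at least one favouring QDP 1−0.975^k.
- k=2: 1−0.95² = 9.75%; 1−0.975² = 4.9%
- k=25: 1−0.975²⁵ = 46.9%
- k=33: 1−0.95³³ = 81.6%; 1−0.975³³ = 56.6%

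For a common correlation ρ between normal test statistics, write each as √ρ·C + √(1−ρ)·E, with C shared and E independent. The favourable-direction rate is 1 − ∫ Φ((1.96−√ρ·c)/√(1−ρ))^k φ(c) dc. The either-direction rate replaces Φ(·) by the probability of lying within ±1.96. Numerical integration gives:

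| Outcomes | ρ | Either direction | Favouring QDP |
|---|---|---|---|
| 2 | 0 | 9.8% | 4.9% |
| 2 | 0.5 | 9.1% | 4.5% |
| 25 | 0 | 72% | 47% |
| 25 | 0.3 | 61% | 32% |
| 25 | 0.5 | 47% | 23% |
| 33 | 0 | 82% | 57% |
| 33 | 0.3 | 69% | 37% |
| 33 | 0.5 | 53% | 27% |
| 33 | 0.7 | 35% | 18% |
| 33 | 0.9 | 18% | 9% |

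The benchmark for the last column is 2.5%, the favourable half of one two-sided 5% test.

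**Cost of the alternatives.** With one primary outcome at 5%, and BMI tested at 5% only after it succeeds, the error for the pair stays at or below 5% and n is unchanged. Splitting alpha at 0.025 each, with the back-solved QoL SD of about 15.95, needs 49 completers, or 49/0.8 → 62 per arm (124 in total). At the planned 40 completers the power for QoL would be about 71%.

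**The case against.** Five points on the other side deserve weight.

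- A reader might infer that a false claim of benefit is likely. The documents do not support that. The 53–82% figures include false results favouring CDC. For results favouring QDP, the rate exceeds one half only if all 33 outcomes are independent. That is not credible: with adult height fixed, change in BMI tracks change in weight, and change in waist-to-height ratio tracks change in waist. For the two sizing endpoints the false-benefit rate is about 4.5–5%.
- A reader might also infer that any of the 33 outcomes could confirm the second hypothesis. It names QoL, adiposity and metabolic parameters, with diet quality as the route; thyroid tests and nutrition knowledge lie outside it. It joins its domains with a conjunction, and nothing states that one significant result suffices. Equally, nothing requires all of them to succeed, so the decision rule is undefined.
- The logistic models do not retest every outcome: thyroid tests and nutrition knowledge are not listed for them.
- For normally distributed variables section 2.12 names a paired t-test, a within-arm comparison. The rates above therefore describe a cleaner, between-arm plan than the one written.
- Multiplicity adjustment of secondary outcomes is commonly left to an analysis plan, and its absence from an article is no finding.

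These points limit the size of the problem. They leave standing two sizing endpoints with no ranking or joint rule, under a blanket p<0.05.

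**Conclusion.** The point holds as a cheap improvement. As written, the rule does not keep the 5% level for the comparison of QDP with CDC. The either-direction error is 9–10% for the two sizing endpoints and 53–82% for 33 outcomes (18% at correlation 0.9). The error in favour of QDP is about 4.5–5% for the two endpoints, 23–47% for the 25 outcomes of the second hypothesis, and 27–57% for all 33 (9% at correlation 0.9).

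The correlations are assumptions, and unless another value is given the ranges run from 0.5 to independence. The figures count one between-arm test per outcome at six months. They leave out the one-month data in Table 1, within-arm tests and the logistic models, each of which could add further chances. The error is well above nominal; whether it passes one half depends on correlations the documents do not give.

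**What to change.** In sections 2.11 and 2.12:

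1. Name overall QoL at six months as the single primary outcome, compared between arms at two-sided 5%.
2. State which ThyPRO measure that is: the single overall-impact item or a stated composite, on the 0–100 scale that the 20/10-point assumption requires. Section 2.7 scores items 0–4 and describes rescaling to 0–100 only for the 13 scales, so a raw item could not fall by 20 points.
3. Test BMI at 5% only if the primary comparison is significant.
4. Replace the blanket significance sentence. Label all other outcomes, including the logistic models, secondary or exploratory, and report them as estimates with 95% confidence intervals and no confirmatory claim.

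Requiring both endpoints to succeed, or splitting alpha, would also be defensible; the choice is the investigators', but it has to be stated. The proposed order takes about a paragraph of text and no extra patients, because overall QoL already fixes 50 per arm. The cost is that fewer outcomes can be called significant.

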### 1.1. Research Objective and Hypothesis

The current state of knowledge related to diet in HT is far from satisfactory, while many HT subjects experience many disorders and report reduced quality of life [13,14,18,23]. There is a strong need to summarize the evidence and develop dietary recommendations that are simple for HT subjects to understand and implement daily over a long-term period, and are useful for dieticians and other health professionals. The conventional approach to dietetic counseling is a structured process aimed at supporting individual patients to modify their dietary behaviors to improve health outcomes [24]. Conventional dietetic counseling is based on the development of individual recommendations and formulating detailed guidelines, which may prove difficult for patients to follow over the long term due to growing fatigue, lowering of motivation, the time required, and difficulties maintaining subject compliance to the diet [25]. Mitchell et al. [24] reported that dietetic counseling appears to be effective, e.g., in improving diet quality, diabetes outcomes, and weight loss outcomes, while limited evidence was found for the effectiveness of direct dietetic counseling alone in achieving outcomes relating to plasma lipid levels and blood pressure. The authors suggested that future research might explore novel nutrition counseling approaches.

There are three aims of the study: (1) to develop a qualitative dietary protocol (QDP; ‘Diet4Hashi’) as a simple, graphic–text tool dedicated TH subjects, (2) to evaluate the use of the QDP in dietetic counseling compared to conventional dietetic counseling (CDC) in HT women, (3) to assess the impact of both the QDP and the CDC on diet quality, quality of life, adiposity, and metabolic parameters. It is planned to develop a food-only protocol without considering the use of supplements because an adequate, well-balanced diet should be the first step in a dietary approach to improving health.

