### 1.2. Study Design

The study is designed as a single-center dietary intervention lasting six months, with a random allocation of HT women into two parallel groups: experimental and control. In the experimental group, the QDP will be applied, while the CDC will be applied in the control group. The QDP is based on subject self-monitoring supported with a graphic–text tool to help them in food selection and adequate food frequency consumption, while the CDC will be supported by an oral explanation and printed sample menus given by dietician. Both approaches include the same dietary recommendations for HT, extracted from the literature, but differ in subject–dietician cooperation. 

The schedule of the enrolment, intervention, and data collection is presented in Table 1. All data will be collected at the same time for both groups, with one exception. The experimental group, supported with a graphic–text tool, will be asked to complete self-monitoring diaries during the six months of the study.

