### 3.3. Strengths and Limitations

The strength of the study was the development of a simple dietary protocol with a user-friendly approach that is easy to use for both individuals with HT and health professionals. This dietary protocol was developed based on scientific evidence and presents the best adherence to current knowledge. Simple markers of adiposity (BMI, WHtR) and metabolic parameters (FBG, TG, TC) useful in dietetic counseling and clinical practice (and easy to replicate in other studies) will be applied. In addition, advanced methods of adiposity measurement (bioelectrical impedance analysis method with an SECA mBCA 525 analyzer) will be applied to accurately measure body composition, including fat mass and skeletal muscle mass. Since the data are experimental observations, the causal effect of dietary intervention can be demonstrated. 

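### Wrong as written: a dependent-samples t-test and a Mann–Whitney test are named as alternatives for change from baseline, so normally distributed outcomes get no QDP-versus-CDC test

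*Protocol article*

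**What the plan says.** The trial is built on a comparison. Section 1.2 describes an intervention "with a random allocation of HT women into two parallel groups: experimental and control". The second aim in Section 1.1 is "to evaluate the use of the QDP in dietetic counseling compared to conventional dietetic counseling (CDC) in HT women", and the hypotheses add that "a better effect of a qualitative dietary protocol than conventional dietetic counseling is possible". Section 2.11 sizes the trial on the expected six-month improvement and "the expected difference between the experimental and the control group": 20 versus 10 points for overall quality of life and 2.0 versus 1.0 kg/m² for BMI.

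Section 2.12 opens with a matching purpose: to assess the impact of counselling and "verify the differences between the experimental and the control group, two-tailed tests will be applied". It then sets a selector: "The normality of variable distribution will be verified with a Kolmogorov–Smirnov test before the statistical analysis". For the continuous variables, which include quality of life scores, adiposity markers and the adherence score (AdhS), "changes after a six-month follow-up with respect to baseline will be verified with a T-test for dependent samples or a Mann–Whitney test", for normal and non-normal variables respectively. Logistic regression is named for categorical variables; the explanatory variable is not stated.

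Section 3.3 concludes: "Since the data are experimental observations, the causal effect of dietary intervention can be demonstrated".

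**The concern.** A dependent-samples t-test compares two measurements on the same women. A Mann–Whitney test compares two separate groups. The usual pairings are dependent t with Wilcoxon signed-rank, or independent t with Mann–Whitney. The plan takes one test from each pair, so the outcome of a normality check changes the question and not only the method.

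For a normally distributed outcome, nothing named in Section 2.12 estimates the difference on which the trial was sized. The analyst is left with one p-value per arm. The natural but invalid step is then to read significance in the QDP arm, or in the QDP arm only, as evidence for the tool. Both arms receive the same dietary recommendations and there is no arm without counselling, so a change within one arm is not protected by randomisation. It would also absorb regression to the mean and any other change over time.

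**Working it through.** **1. Which question does each named test answer?**

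- Normal variable, dependent-samples t-test: is the mean change from baseline in one arm zero? No comparison of arms.
- Non-normal variable, Mann–Whitney on change scores between arms: does change differ between QDP and CDC? This is a valid comparison.
- Non-normal variable, Mann–Whitney on baseline versus six months in one arm: a within-arm question with the pairing ignored. The text does not say which of these two uses is meant.

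**2. AdhS.** Sections 1.2 and 2.4 and Table 1 show that AdhS comes from a diary kept only by the experimental group, during the intervention. It has no baseline and no control value, so neither named test can be applied to it.

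**3. Sample size.** Section 2.11 gives no SD, so its figures cannot be reproduced forwards. They can be inverted with the two-sample formula, n per arm = 2 × SD² × (1.960 + 0.842)² / difference², two-sided 5% and 80% power, after removing 20% dropout:

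- Quality of life: 50 × 0.8 = 40 completers, so SD of change = 10 × √(40/2) / 2.802 = 15.96 points.
- BMI: 42 × 0.8 = 33.6 completers, so SD of change = 1.0 × √(33.6/2) / 2.802 = 1.46 kg/m².

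The stated numbers are therefore compatible with a between-arm calculation. These SDs are assumptions in everything below.

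**4. Paired tests when the arms truly do not differ.** Let p be the probability that a paired t-test on 40 women is significant for a given true improvement (non-central t, 39 degrees of freedom, non-centrality = improvement × √40 / SD). With the same improvement in both arms, the probability that exactly one arm is significant is 2p(1 − p).

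| True improvement in both arms | p (SD 15.96) | Exactly one arm significant (SD 15.96) | Same, SD 14 | Same, SD 18 |
|---|---|---|---|---|
| 0 points | 0.050 | 2 × 0.050 × 0.950 = 9.5% | 9.5% | 9.5% |
| 5 points | 0.489 | 2 × 0.489 × 0.511 = 50% | 48% | 48% |
| 7 points | 0.772 | 2 × 0.772 × 0.228 = 35% | 23% | 44% |
| 10 points | 0.972 | 2 × 0.972 × 0.028 = 5.5% | 1.4% | 13% |

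The expression cannot exceed 50%, which it reaches at p = 0.5, so the 5-point row is the worst case. A two-sample test on change rejects in about 5% of trials in every row.

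**5. Paired tests at the planned effect (20 versus 10 points, SD 15.96).** The QDP test is significant in about 100% of trials and the CDC test in about 97%, so both are significant in about 97%. The pair of results looks the same as when both arms improve by 10 points and do not differ.

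**6. Between-arm test at the planned effect.** With 40 completers per arm and SD 15.96, an independent-samples t-test on change has about 79% power; in simulation Mann–Whitney on change had about 76%.

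**The case against.** Section 2.12 does declare that differences between the arms will be tested. Together with the choice of Mann–Whitney, this suggests that the dependent-samples wording may be a slip for independent samples. That is possible, but nothing else in the article settles it; Wilcoxon signed-rank could equally have been meant in the other branch. The sentence needs correcting either way.

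A within-arm test also has a place: the third aim is to assess the impact of both approaches, and change within each arm speaks to that aim descriptively. This stands, and is why the fix keeps such tests.

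The logistic models might compare arms on categorised outcomes. Even so, they would not supply a test of mean change in quality of life or BMI.

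A reader might infer that the trial has no valid between-arm test at all. The document does not support that: Mann–Whitney on change scores between arms would be valid for non-normal outcomes. A reader might also take the 97% for a paired test at a 10-point improvement as a false-positive rate. It is the power to detect a real change within one arm; the error would lie in reading that change as a difference between arms.

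Finally, the causal sentence in Section 3.3 is defensible for the randomised contrast, and the same section lists the lack of a placebo as a limitation. It is too broad only if it is applied to change within an arm.

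**Conclusion.** The sentence is wrong as written and must be corrected. The two named tests address different hypotheses, a normality pre-test chooses between them, and normally distributed continuous outcomes have no stated QDP-versus-CDC test although the aims, design and sample size rest on that comparison. Whether quality of life and BMI fall into that branch depends on the data.

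The size of the risk depends on the true common change: from about 10% with no change, up to at most 50%, and down to 5 to 6% at 10 points, for a result in which exactly one arm is significant although the arms do not differ. These figures assume normal change scores, 40 completers per arm and the back-calculated SD; the SD range of 14 to 18 moves the 7- and 10-point figures noticeably. The mismatch of the tests does not depend on any of these assumptions.

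**What to change.** Rewrite the continuous-outcome part of Section 2.12:

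- For each continuous outcome measured in both arms at baseline and six months, the main analysis is the between-arm difference at six months with 95% CI, from a linear model with arm, baseline value and the age stratum used in randomisation. At minimum, an independent-samples t-test on change would cure the error.
- A Mann–Whitney comparison of change between arms is a prespecified sensitivity analysis.
- The Kolmogorov–Smirnov test no longer selects the analysis.
- Within-arm change (paired t or Wilcoxon signed-rank) is descriptive only, for the third aim.
- AdhS is summarised descriptively in the experimental arm only.

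In Section 3.3, limit the causal claim to the QDP-versus-CDC contrast.

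The cost is one rewritten paragraph and one edited sentence. Data collection does not change, and under the implied SD the stated sample size gives a between-arm t-test on change about 79% power, so no increase follows from this point.
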